#### Plans to promote participant retention and complete follow-up {18b}

We will distribute a $400 gift card to each participant at the completion of each of the three study conditions. We chose $400 per study condition based on our prior success with recruitment and low attrition with the targeted population [19, 97, 98]. In total, each participant who completes the full study protocol will receive $1200 in remuneration. This amount is less than the total remuneration offered in previous studies with similar protocols and equivalent participant burden [56–58].

#### Data management {19}

All data will be downloaded from monitoring devices, or abstracted from survey instruments, and uploaded to a password-protected REDCap database maintained by the principal investigator’s institution [54, 55].

#### Confidentiality {27}

Confidentiality of study participation will be maintained by storing all paper-based data collection instruments and study-related forms in locked filing cabinets in the locked office of study investigators, located on the University of Pittsburgh campus. All data obtained from electronic devices will be assigned a code number, which will be used to then store participant data electronically in a password-protected REDCap database [54, 55].

#### Plans for collection, laboratory evaluation, and storage of biological specimens for genetic or molecular analysis in this trial/future use {33}

N/A this study protocol does not include the collection of biological specimens.

### Statistical methods

#### Statistical methods for primary and secondary outcomes {20a}

We will report the demographic characteristics of the study sample using descriptive statistics and stratify the final dataset into two categories for the main analysis. These categories will be labeled as “complete” and “incomplete data.” We will further describe the average systolic and diastolic BP, the incidence of blunted BP dipping, and the proportion of participants with blunted BP dipping. Blunted nocturnal BP dipping will be defined as previously described. Our second outcome of interest is HRV. As prescribed [72], we will examine HRV based on five time-based measures summarized over each 24-h period of observation.

To address the impact of napping on BP dipping, we will conduct paired *t* tests to determine if the mean amount of BP dipping differs across conditions. Generalized linear mixed models (GLMM) with participant-specific random effects will be utilized to compare the odds of blunted BP dipping across conditions. We will evaluate the distribution of residuals at each level of the models for linearity and heterogeneity. We will check for outliers and influential observations and sets of observations. The distribution of the data will be examined, and transformations will be performed as necessary for valid comparisons. We will use GLMM to estimate and compare the proportion of EMS workers with blunted BP dipping and control for the dependence between repeated measures within each participant with a random subject effect.

To address the impact of napping on select measures of HRV, we will use GLMM with appropriate distribution and link function to estimate and compare HRV measures between EMS workers across the three conditions. We will again account for the within-participant correlation of repeated measurements and any participant-dependent covariates that vary in the study sample. The least square means and corresponding 95% confidence intervals will be calculated from the models for each group and the difference between groups.

We also plan to compare the slope of HRV and BP amplitude following the simulated shift work across the three conditions. The hypothesis testing will again follow the GLMM framework. Time-varying slopes will be calculated for each participant for the recovery period. These slopes will characterize the change in the outcome measures (HRV and BP amplitude) following shift work. We will account for the within-participant correlation of repeated measurements and any participant-dependent and time-dependent covariates. We will account for actual sleep during the periods of nap opportunity by running multiple statistical models with one set of models standardized for the nap opportunity (i.e., 30 min vs. 120 min) and another set of models that account for the depth of sleep (stage) and the amount of time within each stage of sleep as measured by the Zmachine® Synergy.

Enrollment of 25 participants is projected to provide 80% power to detect a difference in the mean BP dip of 5 mmHg between conditions, assuming two-sided tests, alpha set at 0.05, and a within-participant standard deviation of 6 mmHg (similar to our previous work). Power was calculated using G*Power V3.1.9.2, using two-sided *z* tests in a Poisson regression with alpha set at 0.05.

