### Trial design {8}

We will use a randomized crossover trial study design with three study arms/conditions. All three conditions will involve continuous monitoring over 72 h and will begin with a 36-h at-home period, followed by 24 total hours in the lab (including a 12-h simulated night shift), and ending with 12 h at home. The key difference between the three conditions is the presence or absence of an intra-shift nap and the duration of that nap. Condition 1 will involve a simulated 12-h night shift with no nap: total sleep deprivation. Condition 2 will comprise another simulated 12-h night shift and a 30-min nap opportunity. Condition 3 will involve a simulated 12-h night shift and a 2-h nap opportunity. There will be a mandatory 1–3 week washout period between conditions. The order in which participants complete the study conditions will be balanced by a William’s square design. In the paragraphs below, we outline the details of our experimental study in accordance with the CONSORT/SPIRIT statement. Figure 1 illustrates the flow chart of our trial, and Fig. 2 illustrates the SPIRIT template for enrolment, intervention, and assessment. The University of Pittsburgh Institutional Review Board (IRB) approved this study {24}, and our protocol has been registered with ClinicalTrials.gov ({2a} registration number: NCT04469803; public release date: 9 July 2020). All subjects are required to provide written informed consent (see Additional file 1, which reports on all elements of the SPIRIT checklist). All elements of the World Health Organization Trial Registration Data Set can be found in this article, supplemental file, and the ClinicalTrials.gov registration.

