### Sample size {14}

Our goal enrollment is 35 total participants with an estimated 10 of the 35 enrolled not completing the study protocol or classified as lost to attrition. Our goal for enrollment is based on several factors. (A) Previous research suggests 10–33% [89, 90] of EMS workers will be willing to participate but excluded due to self-reporting a diagnosis of HTN and/or are currently taking medication for HTN. (B) Previous research suggests 10–15% attrition in prospective observational studies [19]. Attrition can impact inferential statistics if participants with complete follow-up data differ from participants who are lost to attrition. Our strategies to address attrition include the following: (A) provide participants with reasonable remuneration and (B) maintain regular communication with participants including, yet not limited to, regular email updates, telephone reminders, text message reminders, and other forms of frequent communication. We will compare available characteristics between those who cease participation and those who complete the study as designed.

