### Sequence generation {16a}

An investigator not overseeing the in-lab sessions will construct the randomization sequence for each participant using the SAS statistical software procedure PROC PLAN (Cary, NC). The sequences will adhere to the Williams design [91], which ensures a uniform crossover design with a balance of order in the experiment as a whole.

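### Paired t tests for mean BP dip cannot adjust for visit order, which the Williams design balances; a mixed model with period is a near-free improvement

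*Protocol article*

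**What the plan says.** Trial design {8} sets the design: "We will use a randomized crossover trial study design with three study arms/conditions". On order it says: "The order in which participants complete the study conditions will be balanced by a William’s square design". The visits are separated in time: "There will be a mandatory 1–3 week washout period between conditions". Sequence generation {16a} repeats the Williams design, "which ensures a uniform crossover design with a balance of order in the experiment as a whole".

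Statistical methods {20a} then names the analyses:

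- **Mean BP dip:** paired t "tests to determine if the mean amount of BP dipping differs across conditions".
- **Blunted dipping (yes/no):** a generalized linear mixed model (GLMM) meant to "control for the dependence between repeated measures within each participant with a random subject effect".
- **HRV and post-shift slopes:** GLMMs that may also take covariates, which are not listed.

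Period and sequence are not named as model terms anywhere. On numbers, Sample size {14} says: "Our goal enrollment is 35 total participants with an estimated 10 of the 35 enrolled not completing the study protocol". The power statement at the end of {20a} uses 25 participants, a 5 mmHg difference in mean dip, a within-participant SD of 6 mmHg and two-sided alpha 0.05, and claims 80%.

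**The concern.** Balancing the order keeps a visit-to-visit trend from favouring one condition. The analysis must also take the trend out of the error, or part of the benefit is lost. A paired t test uses only the within-person differences between two conditions. One participant has the no-nap visit first and the 2-h nap last, and another the reverse, so any trend spreads those differences apart and counts as noise.

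A trend is plausible here. Each participant goes through three 72-h recordings with the same cuff, Holter monitor and laboratory, and the same four types of mock call, one to three weeks apart. The article neither claims nor excludes one. At stake are the precision and power of the mean-dip comparison. If completers end up unevenly spread over the sequences, the estimate can also move somewhat.

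**Working it through.** **Inputs from the article.** n = 25 completers (35 enrolled less 10 lost), difference 5 mmHg, within-participant SD 6 mmHg, two-sided alpha 0.05, three conditions. A three-condition Williams design has six sequences.

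**Assumed input.** The period trend over visits 1/2/3, in mmHg: none, 0/1.5/3, 0/3/6, 0/5/5 and 0/4/8.

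**Step 1: the stated power.** The SD of a within-person difference is 6 × √2 = 8.49, so its variance is 72 and the SE is √(72/25) = 1.70. A paired t test with 24 df then has 80.7% power, and 25 is the smallest n that reaches 80%. The stated 80% therefore reproduces as a paired t test, although the article attributes it to a z test in a Poisson regression. There is no reserve.

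**Step 2: what a trend adds.** Over six equally filled sequences, each pair of conditions falls in each ordered pair of visits once. The variance added to the paired difference is the mean of the six squared visit differences:

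- 0/1.5/3: (4 × 1.5² + 2 × 3²)/6 = 4.5
- 0/3/6: (4 × 3² + 2 × 6²)/6 = 18
- 0/5/5: (4 × 5² + 2 × 0²)/6 = 16.7
- 0/4/8: (4 × 4² + 2 × 8²)/6 = 32

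The paired t test works with SE = √((72 + added variance)/25). The true spread of the estimate under balance stays at 1.70. The test therefore overstates its own error, which makes it conservative. As an approximation, with critical value 2.064, power ≈ Φ((5 − 2.064 × SE)/1.70).

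**Step 3: power and type I error.** Type I error and the simulated powers come from simulation with the six sequences filled in blocks. The comparison model has participant, period and condition terms.

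| Trend | Paired-t SE | Power by formula | Power simulated | Power with period in model | Type I error, paired t |
|---|---|---|---|---|---|
| none | 1.70 | 81% | 81% | about 82% | 5% |
| 0/1.5/3 | 1.75 | 79% | 79% | about 82% | about 4% |
| 0/3/6 | 1.90 | 74% | 73% | about 82% | 3% |
| 0/5/5 | 1.88 | 74% | 74% | about 82% | 3–4% |
| 0/4/8 | 2.04 | 68% | 67% | about 82% | about 2% |

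The last row averages over the sequence that the 25th completer happens to have. If that person had no nap first and the 2-h nap last, a shift of 8/25 = 0.32 mmHg favours the difference, and power is about 72%.

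**Step 4: degrees of freedom.** The model has 25 × 3 = 75 observations. Subtracting 25 for participants and 2 for condition leaves 48. Subtracting 2 more for period leaves 46. A paired t test has 24. With 46 df and no trend, power is 82.2%.

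**Step 5: imbalance after dropout.** If a random 25 of 35 complete, the trend shifts the unadjusted difference between two conditions. The 95th percentile of the absolute shift is 0.48 mmHg for 0/1.5/3, 0.80 for 0/5/5 and 0.96 for 0/3/6. Averaged over randomization the shift is zero. With period in the model it disappears.

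**The case against.** The strongest reply is that the paired t test is valid here. The order is randomized, the test errs on the safe side, and the loss exists only if there is a trend, which the article does not report. All of that stands. With no trend, the two analyses differ by about one percentage point of power. The 0/4/8 case is also severe: its total exceeds both the 5 mmHg target and the 6 mmHg SD. A paired t test further avoids assuming equal variances across the three conditions, which the simplest mixed model makes. That can be checked and relaxed.

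A reader might infer four stronger things, and the article supports none of them.

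- **Inflated false positives.** Type I error falls when period is left out. What rises is the SE and the type II error.
- **Bias because the numbers are not multiples of six.** It is true that 25 = 4 × 6 + 1 and 35 = 5 × 6 + 5. With filled blocks and a 0/3/6 trend, however, the shift is at most 6/25 = 0.24 mmHg, or 6/35 = 0.17 mmHg, against a 5 mmHg target.
- **Systematic bias from dropout.** This needs dropout that depends on sequence. Nothing in the article shows it, and under Concealment mechanism {16b} each visit's condition is revealed only when that session begins.
- **All models lack period.** Only the blunted-dipping GLMM is described with nothing beyond a random subject effect. The HRV and slope models allow unlisted covariates, and a fuller analysis plan may name period. The paired t test is different: it is fixed here in a form that cannot take the term.

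**Conclusion.** The point holds as an improvement in efficiency. It is not an error that makes the results invalid. The named test for mean dip does not use the balance that the design provides. If a period trend exists, the cost is precision: at 0/3/6 mmHg the variance of the paired difference rises from 72 to 90 and power drops from about 81% to 73%, below the planned 80%. If no trend exists, almost nothing is lost. The chance bias of about 0.5 to 1 mmHg is the 95th percentile under trends of 0/1.5/3 to 0/3/6 and random loss of 10 of 35. It is not an expected value.

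These figures assume the article's SD of 6 mmHg, equal variances across conditions, an additive trend common to all participants, and trend sizes that are not in the article.

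**What to change.** In Statistical methods {20a}, replace the paired t tests with one linear mixed model for BP dip, with condition and period (visit 1, 2, 3) as fixed effects and participant as a random effect. Report all three condition contrasts with 95% confidence intervals from that model. State that period is also a fixed effect in the GLMMs for blunted dipping and for SDNN.

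The change uses visit order, which is already recorded, and needs only wording and model code. The price is two degrees of freedom for period, and the pooled model still has 46 against 24 for each paired t test.

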### Outcomes {12}

Our primary outcomes of interest include blunted BP dipping and reduced HRV as measured by the standard deviation of the inter-beat intervals of normal sinus beats (SDNN). Blunted BP dipping will be calculated using two measures. First, we will quantify sleep vs. wake BP dipping by identifying the participant’s sleep and wake times and stratifying the hourly ABPM measures into sleep vs. wake measures. The ratio of sleep-to-wake BP is calculated by taking the difference between the mean systolic and diastolic BP during the sleeping hours and the mean systolic and diastolic BP during waking hours. We define dipping status as follows: (mean wake hours BP − mean sleep BP divided by mean wake hours BP) × 100. Non-dipping status will be defined as sleep hours BP dip of less than 10%, assessed with systolic BP (SBP) and diastolic BP (DBP) [22, 69]. Next, we will stratify each 24-h period into nighttime vs. daytime periods and calculate nighttime BP dipping with the “wide fixed time method” [70, 71]. Daytime hours are defined as 0700 to 2259 h, and nighttime hours are defined as 2300 to 0659 h [70, 71]. The ratio of night-to-day BP is determined by taking the difference between the mean systolic and diastolic BP during the nighttime hours (2300 to 0659 h) and the mean systolic and diastolic BP during daylight hours (0700 to 2259 h). For this method, nighttime dipping status is determined as follows: ((mean daylight BP − mean nighttime BP) ÷ mean daylight hours BP) × 100. We will assess dipping vs. non-dipping status during sleep hours and during nighttime hours for all periods of observation and for all study conditions.

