Our second outcome of interest is reduced HRV. As prescribed [72], we will examine HRV based on five time-based measures summarized over each 24-h period of observation. Measures include the following: (A) standard deviation of the inter-beat intervals of normal sinus beats (SDNN) summarized over 24 h; (B) standard deviation of the averaged normal sinus intervals for all 5-min segments (SDANN) summarized over 24 h; (C) the mean of the standard deviations of all normal sinus RR intervals for all 5-min segments (SDNN index) summarized over 24 h and stratified by wake, sleep, and work and non-work periods; (D) root-mean-square of the successive normal sinus RR interval difference (rMSSD) summarized over 24 h; and (E) the low-frequency (LF) band and high-frequency band (HF) ratio (LF/HF) summarized over 24 h and stratified by wake, sleep, and work and non-work periods. The LF/HF ratio is a frequency domain measure of HRV that depicts the balance between sympathetic and parasympathetic activity of the nervous system [41]. Low values reflect the dominance of the parasympathetic system whereas a high ratio is indicative of sympathetic dominance [41]. For medical risk stratification, the SDNN over a 24-h period is considered a gold standard measure [41]. Twenty-four-hour measures of SDNN < 50 ms are considered unhealthy [41, 73, 74].

We will administer multiple survey instruments at baseline and during the study period, including a standard demographics survey. At baseline, we will administer the Pittsburgh Sleep Quality Index (PSQI), which we will use to measure sleep quality [75]. The Epworth Sleepiness Scale (ESS) will be used to measure daytime sleepiness [76]. The Chalder Fatigue Questionnaire (CFQ) will measure mental and physical fatigue [77]. With permission from the developer, we will use the Occupational Fatigue and Recovery (OFER) Scale to assess acute fatigue, chronic fatigue, and inter-shift recovery [78]. The Copenhagen Burnout Inventory (CBI) will measure burnout [79]. Five items from the Schedule Attitudes Survey (SAS) will measure satisfaction with shift schedule [80].

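### Where a 72-h session contributes more than one value to a condition contrast, a random subject effect alone leaves out session-to-session variation, and the false-positive rate exceeds 5%

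*Protocol article*

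**What the plan says.** All places are in the protocol article.

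- **Design.** Trial design {8} makes each condition one 72-h session, with 1 to 3 weeks of washout between sessions. Within a participant, condition and session therefore coincide.
- **Dipping outcome.** Outcomes {12}: "We will assess dipping vs. non-dipping status during sleep hours and during nighttime hours for all periods of observation and for all study conditions".
- **HRV outcome.** Outcomes {12}: "we will examine HRV based on five time-based measures summarized over each 24-h period of observation". A 72-h session can thus give up to three values.
- **Dipping model.** Statistical methods {20a} uses a GLMM to compare the proportion with blunted dipping and to "control for the dependence between repeated measures within each participant with a random subject effect". An earlier sentence there speaks of participant-specific random effects in the plural, without listing them.
- **HRV model.** {20a} says that within-participant correlation will be accounted for and names no structure.
- **Recovery model.** {20a} compares slopes after the shift: "The hypothesis testing will again follow the GLMM framework". BP is read hourly ({18a}).
- **Mean dip.** {20a} uses paired t tests across conditions.

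No session or participant-by-condition term is named anywhere, and the number of values per session entering each model is not stated.

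**The concern.** A random subject effect makes all values from one person equally alike, whether they come from the same session or from sessions weeks apart. If a person's sessions differ for reasons unrelated to the nap, values from one session move together, and so do values under one condition. The correct yardstick for a condition contrast is the variation of session means within a person. A subject-only model fed several values per session uses mostly the smaller scatter within sessions. A fixed period effect does not help, because the missing component is specific to each participant and session.

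The odds of blunted dipping and SDNN are primary outcomes, so confidence intervals that are too narrow would lead to nap effects being declared too often in a trial expecting 25 completers.

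**Working it through.** **1. The plan's own figure.** The inputs from {20a} are a two-sided 5% level, an SD of 6 mmHg within a participant, and this target: "Enrollment of 25 participants is projected to provide 80% power to detect a difference in the mean BP dip of 5 mmHg between conditions". The number of completers follows from Sample size {14}, which allows for 10 losses among 35 enrolled: 35 − 10 = 25. With one value per participant per condition:

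- SD of a paired difference = 6 × √2 = 8.49 mmHg
- noncentrality = 5 / 8.49 × √25 = 2.95
- power of the two-sided paired t test (24 df) = 80.7%

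The 80% is reproduced on the basis of one value per session.

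**2. Continuous outcome, m values per session.** Set the within-person variance to 1 and let rho be the share lying between sessions. Rho is not in the document, so a range is used. With n = 25 and three conditions:

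- mean square that the condition contrast should use: T = m·rho + (1 − rho)
- mean square that the subject-only model uses, in expectation: M = [48·T + 75(m − 1)(1 − rho)] / [48 + 75(m − 1)], where 48 = 2 × 24 and 75 = 25 × 3
- false-positive rate of a pairwise test ≈ 2·[1 − Φ(t_crit / √(T/M))]

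For m = 3 there are 48 + 150 = 198 df and t_crit = 1.972.

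| rho | T | M | √(T/M) | Formula | Simulated (8,000 runs) |
|---|---|---|---|---|---|
| 0.1 | 1.2 | 0.973 | 1.11 | 7.6% | 7.6% |
| 0.2 | 1.4 | 0.945 | 1.22 | 10.5% | 11.1% |
| 0.3 | 1.6 | 0.918 | 1.32 | 13.5% | 13.9% |
| 0.5 | 2.0 | 0.864 | 1.52 | 19.5% | 19.5% |

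Separate simulations give about 7 to 21% over the same range of rho. With two values per session the simulated pairwise rates are 6.8, 8.0, 9.0 and 13.6%. The omnibus three-condition test is worse at m = 3: 8.6 to 27.2%.

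With m = 1, T = M and the simulated rate is about 5% at every rho. With rho = 0 it is about 5% at every m. Analysing session means at m > 1 gives 4.7 to 5.3% throughout.

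**3. Binary blunted dipping.** Random-intercept logistic model, likelihood-ratio test across three conditions, n = 25, 600 runs per cell (Monte Carlo error about 1 to 2 points), subject SD 1 on the logit scale:

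| Values per session | Session SD 0 | Session SD 1.0 | Session SD 1.8 |
|---|---|---|---|
| 1 | 5.3% | 4.8% | 5.0% |
| 2 | 5.0% | 9.3% | 12.0% |
| 3 | 5.2% | 11.7% | 21.5% |

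**4. Recovery slope.** Hourly BP from 0700 to 1900 in the laboratory plus 12 h at home gives 12 + 12 = 24 scheduled readings. Assumed: residual SD 10 mmHg and session intercept SD 4 mmHg. The pairwise condition-by-time test with a subject effect only (4,000 runs) rejects in:

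- 9% with session slope SD 5 mmHg per 24 h
- 21% with session slope SD 10 mmHg per 24 h
- 20% with residual autocorrelation 0.5 and no slope variation

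Across separate runs of these settings the range is about 8 to 24%. A paired t test on one slope per session holds 4 to 5% in all three.

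**The case against.** The strongest reply is that the document never says several values per session go into one condition contrast.

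- In a three-condition crossover, repeated measures can simply mean the three conditions. The modelled quantity is a proportion of workers, the companion analysis is a paired t test, and the power figure reproduces with one value per condition.
- Outcomes {12} defines what is measured, not what is stacked in a model. Pooling the 36 h at home before the shift with the shift itself would be odd.
- For HRV and recovery the correlation structure is open. A slope calculated per participant may already be a one-number summary. Such details often sit in an analysis plan that is not shown.

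Much of this stands. A reader might infer that inflation is certain and reaches both primary outcomes and recovery. The documents do not support that: the explicit random-subject wording covers only blunted dipping, and one value per session keeps the error rate near 5%. A contrast confined to one period would also be affected much less than a pooled one. A reader might take the 6 mmHg SD as evidence of session variation. It does not separate variation between sessions from variation within them, so it does not identify rho. A reader might also quote rates of 30 to 42% for a mean level over 24 hourly values (rho 0.1 to 0.2), but {20a} compares slopes in recovery, not mean levels.

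What the reply does not remove: for dipping, {20a} states a dependence structure rather than leaving it open, and {12} describes several dipping and HRV values per session. A slope needs at least two readings per session. Following the text with those values in one model gives the wrong error term.

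**Conclusion.** The point holds conditionally. A subject-only model is adequate for one value per participant per condition, and the paired t tests are unaffected when used that way. Once a session contributes more than one value to a condition contrast and sessions differ within a person, the nominal 5% is exceeded by the amounts shown above: modestly if sessions carry little of the within-person variance, and up to roughly four times nominal at a share of 0.5 with three values. The binary and recovery-slope results are of similar size. All of these rest on assumed variance components, and the number of values per model is also assumed. It merits a change before analysis because it touches the primary dipping comparison and the change is small.

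**What to change.** In {20a}, state how many values per session enter each GLMM, then use one of two forms.

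1. **Several values per session:** specify a random subject effect plus a random session (participant-by-condition) effect. For serial recovery data, add a session-level random slope and autocorrelated residuals within session.
2. **One value per session:** reduce each session to one dip, one SDNN or one recovery slope, and keep the random subject effect.

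The cost is a line of wording and an extra random term, with no new data. Confidence intervals will be wider where several values are used. The binary model may fail to converge with the extra term, so name the one-value-per-session form in advance as the fallback.
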